### Statistical analysis

The statistical analysis will be conducted using SPSS 15.0 in Windows. In order to verify data normality, the Shapiro-Wilk test will be used. A comparison of the variables of muscle strength, functional capacity and plasma levels of IL-6 and TNF-α, before and after the intervention and three months after the completed intervention, will be conducted using ANOVA. A post hoc analysis will be conducted to find possible differences. A correlation among the variables will be analyzed using the test of Pearson's correlation. An association among the variables of IL-6 and TNF-α plasma levels, functional capacity and muscle strength will be analyzed using a linear regression. The significance level will be p = 0.05.

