**Methods/Design:**

The study design is a randomized crossover clinical trial evaluating 26 elderly women (regardless of their race and/or social condition) who are community residents, older than 65, and classified as pre-frail according to the criteria previously described by Fried et al. (2004). All subjects will be assessed using the Timed up and go and 10-Meter Walk Test functional tests. The plasma levels of IL-6 and TNF-α will be assessed by ELISA (*enzyme-linked immunosorbent assay*) with high sensitivity kits (Quantikine^®^HS, R&D Systems Minneapolis, MN, U.S.). Knee extensor muscle strength will be assessed using the *Byodex System 3 Pro*^*® *^isokinetic dynamometer at angular speeds of 60 and 180°/s. The intervention will consist of strengthening exercises of the lower extremities at 50 to 70% of 1RM (maximal resistance) three times per week for ten weeks. The volunteers will be randomized into two groups: group E, the intervention group, and group C, the control group that did not initiate any new activities during the initial study period (ten weeks). After the initial period, group C will begin the intervention and group E will maintain everyday activities without exercising. At the end of the total study period, all volunteers will be reassessed.

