## Methods/Design

The general objective of the study will be verified the effect of a program of resistance exercises at 75% RM on the functional capacity, knee extensor muscle strength, and to measure the plasma levels of IL-6 and sTNFr in pre-frail elderly women.

Questions/Hypotheses

1. Among pre-frail elderly women, will changes occur in the plasma levels of the inflammatory mediators IL-6 and sTNFr, functional capacity and knee extensor muscle strength after completing a program of resistance exercises at 75% of 1RM, three times a week, for 10 weeks?

2. In a follow-up three months after finishing the training, will there be modifications in the functional capacity, knee extensor muscle strength and the plasma levels of IL-6 and sTNFr in pre-frail elderly women?

3. Is there a correlation between functional capacity, knee extensor muscle strength and plasma levels of IL-6 and sTNFr before and after a training program with load in pre-frail elderly women?

The study design is a blind randomized crossover clinical trial. Participants will be recruited from two universities. An initial assessment will be undertaken after recruitment and prior to randomization into either experimental or control group. Participants in the experimental group will receive an exercise program, three times a week, during ten weeks. Participants in the control group will receive no physiotherapy intervention. Outcomes will be measured again after ten weeks to reflect the immediate effect of the intervention. Then, the experimental group will receive no physiotherapy intervention and the control group will receive the same exercise program. Outcomes will be measured again to reflect longer-term outcomes from experimental group and the immediate effect of the intervention in the control group (Figure 1). This allows verification of the existence of a change and/or variable correlations specifically due to the intervention, and not due to the time factor and/or changes in the aging process. Furthermore, it allows verification of the existence of variable changes after finishing the training. Additionally, from an ethical point of view, it guarantees that the volunteers receive the same treatment. The outcome measures will be collected by a physiotherapist who was blind to group allocation. The responsible for the intervention will not know about the assessment. The study was approved by the ethical committee of the university and informed consent procedures were taken.

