### Sample

Twenty-six women, regardless of their race and/or social class, above the age of 65 who are community residents and classified as pre-frail according to the criteria established by Fried et al. (2001) will be selected for inclusion in the study. These volunteers will be randomly divided into two groups (control = C and experimental = E) of 13 volunteers each. This population was chosen based upon the assumption that pre-frail elderly people appear to respond better to interventions, resulting in a greater possibility of modifications that influence muscle response.^3 ^Demographic characteristics (age, race, school level, height, weight and body mass index) will be collected from all the participants.

Elderly women who meet one or more of the following criteria will be excluded from the study: previous lower extremities orthopedic surgery, a history of fractures within the past year, an inability to walk unaided, carriers of neurological diseases, diagnosed acute inflammatory disease that could interfere in the assessments and the program, tumor growth in the last five years, current use of immunomodulating medications and cognitive impairment based on the mini-mental state examination [31].

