### Sample size

The sample size was calculated after a previous pilot study with 12 participants, considering a confidence interval of 95%, a bilateral hypothesis test, a significance level of 0.05 (type I error), a power of 80% (type II error) and a crossover design for a statistical analysis of ANOVA. First, we calculated the size effect (f) for the partial ANOVA for the 12 participants, according to Portner & Watkins [39]. We use the functional performance (time in seconds of the TUG). We considered two freedom degrees and a power of 80%. It was determined that, considering a moderate effect size (0.5) for a minimum clinically significant difference, 13 volunteers will be needed in each group.

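### A three-occasion ANOVA, run in its standard repeated-measures form, would discard the baseline and week-10 data of any woman who misses the last visit

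*Protocol article*

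**What the plan says.** **Analysis.** The Statistical analysis section of the protocol article names SPSS 15.0 and one method for the main comparison. Strength, function and cytokines "before and after the intervention and three months after the completed intervention, will be conducted using ANOVA", followed by post hoc tests. The article does not say whether the ANOVA is repeated-measures, or how a woman with a missing occasion is treated.

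**Clues to the form.** The Sample size section describes a crossover design analysed by ANOVA and adds: "We considered two freedom degrees and a power of 80" per cent. It ends: "considering a moderate effect size (0.5) for a minimum clinically significant difference, 13 volunteers will be needed in each group".

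**Enrolment.** The Sample section has 26 women "randomly divided into two groups (control = C and experimental = E) of 13 volunteers each", which is the calculated number with no visible addition for losses.

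**Visits.** Everyone is measured at baseline and again at ten weeks. The Abstract adds: "At the end of the total study period, all volunteers will be reassessed". Under Methods/Design and Intervention, group E trains in the first ten weeks, and group C starts the same programme after the ten-week assessment while E stops.

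**The concern.** Up to week 10 the trial is a plain two-group randomised comparison: E has trained, C has not, and nothing can carry over. It is the cleanest estimate of the training effect the design offers. The final visit still compares randomised groups, but by then both have trained and the contrast is between sequences.

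The usual repeated-measures ANOVA needs a value at every occasion. A woman measured at baseline and week 10 who misses the last occasion is removed entirely, so a later event deletes a week-10 result already in hand. Two things are at stake:

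- **Precision.** The trial is small, and enrolment equals the number said to be needed.
- **Comparability.** After week 10 the groups face different demands: C has 30 sessions ahead and E has none. Reasons for missing the last visit may therefore differ by group, and deletion would carry that difference back into the week-10 comparison. The article gives no basis for saying in which direction.

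**Working it through.** **1. Which ANOVA does the plan's own calculation fit?**

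Inputs from Sample size: effect size f = 0.5, two-sided alpha 0.05, power 80%, 2 degrees of freedom, 13 per group. Power is taken from the noncentral F distribution with noncentrality λ.

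| Reading | df | λ | Power at the planned size | Size for 80% |
|---|---|---|---|---|
| One-way, 3 levels, 13 per level | 2, 36 | 0.25 × 39 = 9.75 | 76.9% | 14 per level (80.3%) |
| 2 groups × 3 occasions, interaction, 26 women, λ = f² × df2 | 2, 48 | 0.25 × 48 = 12 | 86.1% | 23 in total |
| 2 groups only, 13 per group | 1, 24 | 0.25 × 26 = 6.5 | 68.7% | 17 per group |

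No reading gives exactly 13 at 80%. The three-level reading comes closest, at 14. A two-group comparison has 1 degree of freedom, whereas three occasions, or group by three occasions, have 2. The stated 2 therefore match the three occasions in the Statistical analysis section. Since the same women are measured each time, a within-woman factor is the natural reading. This is an inference; the article does not name the form.

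**2. What complete-case deletion costs at week 10**

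Assumption: 2 or 3 women per group miss the last occasion but have week-10 values. The information in a two-group difference is proportional to n1·n2/(n1 + n2). With 13 v 13 this is 169/26 = 6.5.

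| Left after deletion | n1·n2/(n1 + n2) | Information kept | SE multiplier |
|---|---|---|---|
| 11 v 11 | 121/22 = 5.50 | 5.50/6.5 = 84.6% | √(13/11) = 1.087 |
| 10 v 10 | 100/20 = 5.00 | 5.00/6.5 = 76.9% | √(13/10) = 1.140 |
| 13 v 11 (2 lost, one group) | 143/24 = 5.96 | 91.7% | √(6.5/5.96) = 1.044 |
| 13 v 10 (3 lost, one group) | 130/23 = 5.65 | 87.0% | √(6.5/5.65) = 1.072 |

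Losing 2 to 3 per group thus costs 15% to 23% of the information, and the standard error grows by 9% to 14%. Losses in one group only cost 8% to 13%, with the standard error up 4% to 7%.

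**3. In terms of power**

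With two groups, f = 0.5 is a standardised difference d = 2f = 1. For a two-sided t test at 0.05 with noncentrality d/√(1/n1 + 1/n2), power is 68.7% at 13 v 13, 60.7% at 11 v 11 and 56.2% at 10 v 10. These show the relative cost; the article does not present its power figure as that of a week-10 t test.

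**4. Does the calendar matter?**

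The listed occasions are before, after and three months after training. The last described visit follows the second ten-week period: ten weeks after E's training, and straight after C's. The two descriptions do not match. Whichever is meant, the third occasion falls after week 10 in both groups, so a rule requiring all three makes use of a woman's week-10 value depend on a later visit.

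**The case against.** **The deletion rule is not written down.** The article says only ANOVA with post hoc tests. It gives no complete-case rule, and separate week-10 tests could still use the earlier data. A journal article may also leave missing-data handling to a fuller document. This stands, and it limits the point. What the article does fix is an ANOVA over three occasions on the same women, and the usual form of that method deletes incomplete records. Naming a better method is more than asking for a policy to be written down.

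**The loss rates are assumed.** They are. If nobody misses the last visit, nothing is lost.

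**A stronger reading is tempting.** A reader might infer that the analysis is confined to women who completed training. Question 1 asks about changes "after completing a program of resistance exercises at 75% of 1RM, three times a week, for 10 weeks", and the Intervention section describes group E at the switch as having completed the programme. Since C has no programme to complete in the first ten weeks, such a restriction would remove women from E alone and might flatter training. The document does not support this. The wording reads naturally as timing or as a label for the group, no sentence excludes a woman who stops training, and the visit plan reassesses everyone. C also trains in the second period, so a completer rule would not touch E only over the whole trial. Nor is a direction of bias established: it depends on an assumed link between stopping and outcome, and in an analysis of change from baseline it could run against training.

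**Conclusion.** The point holds in limited form. The analysis named, in its standard repeated-measures version, would let a missed last visit erase baseline and week-10 data from the comparison that precedes the crossover. The cost is 15% to 23% of the week-10 information (standard error up 9% to 14%) if 2 to 3 women per group are lost late, and less if the losses fall in one group.

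This rests on two things the article does not state: that the ANOVA is repeated-measures on complete records, which the two degrees of freedom and crossover design suggest, and that losses of this size occur. Different reasons for late loss in E and C are plausible because only C trains in weeks 10 to 20; no size or direction can be given. A completers-only analysis and a bias in favour of training are not part of this conclusion.

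**What to change.** In the Statistical analysis section:

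- Replace the three-occasion ANOVA with a likelihood-based linear mixed model with group, occasion and group by occasion, fitted to all available records, including those of women with a missing occasion.
- State that the week-10 E-versus-C comparison includes every randomised woman with a week-10 value, in her allocated group, whatever her attendance at training or at later visits.
- Give the occasions in the model as study weeks, so that the third one is the same in the analysis and the visit plan.

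The cost is a change of wording and a different procedure in the same software, with slightly more analysis work. The mixed model assumes that missing values are missing at random given the values observed. That cannot be verified from the data. No extra visits or measurements are needed.

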### Randomization

After the initial evaluation, the volunteers will be randomized into either group E or group C. This randomization will take place with an equal number of envelopes. The researcher responsible for the evaluations will be blinded to the participants' group. The researcher responsible for the intervention will be blinded to the assessment results until the final data collection.

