After ten weeks, all the volunteers will be reevaluated with the same tests and parameters conducted in the first assessment. After this reevaluation, the groups will switch and those women who had completed the exercise program (experimental group) will now remain inactive. Those women who had previously been inactive (control group) will begin the same resistance program the experimental group had performed (Figure 1).

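### The Statistical analysis section uses each pre-randomisation value only as an ANOVA occasion and states no baseline covariate; ANCOVA at week 10 would gain about 0 to 16 points of power at almost no cost

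*Protocol article*

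**What the plan says.** The Methods/Design section fixes when the first measurement is taken: "An initial assessment will be undertaken after recruitment and prior to randomization into either experimental or control group". The Intervention section then says "After ten weeks, all the volunteers will be reevaluated with the same tests and parameters conducted in the first assessment". Every outcome, including the primary IL-6 and TNF-α, therefore has a pre-randomisation value and a week-10 value from the same test.

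The Statistical analysis section says the comparison of strength, functional capacity and cytokines "before and after the intervention and three months after the completed intervention, will be conducted using ANOVA", followed by post hoc tests. This gives the first measurement one role, as the earliest occasion of the ANOVA. No covariate is stated. The linear regression in the same paragraph concerns associations among the outcomes and does not adjust a training effect.

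On allocation, the Randomization section says "This randomization will take place with an equal number of envelopes" and describes nothing that balances the groups on baseline level.

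**The concern.** Week 10 is the visit at which trained women (group E) can be compared with randomised women who have not yet trained (group C). Even if the ANOVA is read favourably, as a group-by-time test on the baseline and week-10 visits, it amounts to comparing raw changes. That subtracts the whole of the baseline value whatever the correlation between visits, whereas a covariate subtracts only the part that predicts the later value. When the correlation is modest, as it could be for cytokines, subtracting all of it adds noise.

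With 26 women, precision is scarce. The baseline measurement is already being collected, and using it less efficiently makes a real effect on the primary outcomes easier to miss. In groups of 13, chance baseline differences are also not small, and the change score over-corrects for them.

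**Working it through.** **Inputs.** From the Sample size section: 13 women per group, "a bilateral hypothesis test", "a significance level of 0.05 (type I error", and "considering a moderate effect size (0.5) for a minimum clinically significant difference". The 0.5 is introduced as f, which for two groups means d = 2f = 1.0. Because it is labelled moderate, d = 0.5 is carried as an alternative reading. The baseline to week-10 correlation rho is not given, so it is assumed over 0.3 to 0.9. No dropout is assumed.

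**The plan's own figure.** A one-way ANOVA with f = 0.5, two numerator degrees of freedom and three independent cells has 76.9% power at 13 per cell and 80.3% at 14. This comes within one woman per cell of the stated 13, though it is not the two-group crossover design. With two groups, f = 0.5 and 13 each, power is 68.7%.

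**Change score (two-visit group-by-time).** The variance of a woman's change is 2(1 − rho) in units of the outcome variance. The standardised effect is d / √(2(1 − rho)), with 24 df.

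**ANCOVA.** The residual variance is 1 − rho², multiplied by 1 + 1/22 = 23/22 for estimating the slope with a random covariate. The standardised effect is d / √((1 − rho²)·23/22), with 23 df.

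**Example, d = 1.0 and rho = 0.5.** Change score: 2(1 − 0.5) = 1.00, effect 1.000, power 68.7%. ANCOVA: 0.75 × 23/22 = 0.784, effect 1.129, power 78.7%. The gain is 10 points. A simulation of 20,000 trials gave 68.3% and 78.6%.

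**Over the range** (two-sided noncentral t, 13 per group, power in %):

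| rho | d = 1.0: change | d = 1.0: ANCOVA | gain | d = 0.5: change | d = 0.5: ANCOVA | gain |
|---|---|---|---|---|---|---|
| 0.3 | 54.3 | 70.7 | 16.4 | 17.9 | 24.0 | 6.2 |
| 0.5 | 68.7 | 78.7 | 10.1 | 23.2 | 28.1 | 5.0 |
| 0.6 | 78.1 | 84.7 | 6.6 | 27.8 | 32.1 | 4.3 |
| 0.7 | 88.4 | 91.7 | 3.2 | 35.2 | 38.7 | 3.5 |
| 0.8 | 97.2 | 97.8 | 0.7 | 49.0 | 51.2 | 2.2 |
| 0.9 | 100.0 | 100.0 | 0.0 | 78.1 | 78.2 | 0.1 |

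Gains are computed before rounding. At d = 1.0 and high rho, part of the shrinkage is a ceiling effect, since both powers approach 100%.

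**Where the advantage ends.** (1 − rho²)·23/22 < 2(1 − rho) reduces to 1 + rho < 2 × 22/23, that is rho < 0.913.

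**Chance imbalance.** The baseline difference between two groups of 13 has SD √(2/13) = 0.39 outcome SDs, and exceeds 0.5 SD in either direction in 20% of randomisations. Given an imbalance, the change-score estimate shifts by (rho − 1) times its size. For 0.5 SD at rho = 0.5 this is −0.25 SD.

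**Three-occasion ANOVA.** By simulation at d = 1.0 and rho = 0.5, with group C trained by the third visit, the group-by-time test has about 73% power if group E keeps its whole gain, roughly 6 points below ANCOVA at week 10 (about 79%). If group E loses its whole gain, the test has over 99%, which is above ANCOVA.

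**The case against.** The strongest reply is that this is one paragraph of a journal article and that covariates are commonly left to a fuller plan. That is a fair limit: the article states no covariate, but a reader who infers that baseline adjustment is ruled out goes beyond the text. What remains is that the paragraph does assign the baseline a role, as an occasion of the main comparison, and that a better use of it is available.

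A reader might also infer a fixed loss of about 10 points for every outcome. The document does not support this. The figure needs rho = 0.5, d = 1.0 and the two-visit reading. The effect size was set for the Timed Up and Go, for which the Secondary outcomes section quotes reliabilities of 0.99 and 0.93; it also quotes 0.99 for the dynamometer. Reliability is not a ten-week correlation in a trial where women train, but it serves as a rough upper guide. If the correlations come near those values, the gain for these outcomes is close to nil, and above 0.91 ANCOVA is marginally less precise. It is therefore not better for every rho below 1. For the cytokines the article gives neither a repeatability figure nor an effect size, so the size of their gain is unknown.

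It is also tempting to say that imbalance will produce false positives. Under randomisation the change-score test is unbiased on average and keeps its 5% error rate. The 0.25 SD shift is conditional on the imbalance that happens to occur.

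Finally, the three-occasion ANOVA can beat ANCOVA when the training gain is lost. That stands as arithmetic, but the advantage depends on the answer to the article's own second question, whether the gain lasts. It also mixes that question with the week-10 effect.

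**Conclusion.** The point holds as an inexpensive improvement to the analysis; it does not make the planned ANOVA invalid. For the week-10 comparison of E with C at 13 per group, ANCOVA is more efficient than the two-visit group-by-time test for rho below about 0.91. The gain runs from about 16 points (rho = 0.3) to none (0.9) if the stated effect size means d = 1.0, and from about 6 points to none if it means d = 0.5. These figures assume equal variances at both visits, a linear relation between them and no dropout. Against a three-occasion ANOVA the comparison can go either way. The case is strongest for IL-6 and TNF-α, because they are primary and nothing in the article suggests that their correlation is high enough to make the choice immaterial.

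**What to change.** In the Statistical analysis section, state that the week-10 training effect on each outcome, with IL-6 and TNF-α as primary, is estimated by a linear model of the week-10 value on randomised group (E or C). The covariate is the woman's own pre-randomisation value of the same variable, on the same scale as the outcome. Report the adjusted mean difference with its 95% confidence interval.

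Keep the post-training follow-up (question 2 in Methods/Design) and group C's training period as separate, named analyses, since the week-10 model answers neither.

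The change needs no new data or visits and runs in the SPSS version already named. It costs one residual degree of freedom (24 to 23), and it brings little or nothing for any outcome whose correlation proves very high.

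### The only stated effect comparison is before, after and three months after the intervention, with no term for the randomised groups, so as written it cannot separate training from time

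*Protocol article*

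**What the plan says.** Statistical analysis section: muscle strength, functional capacity and the two cytokines are to be compared "before and after the intervention and three months after the completed intervention, will be conducted using ANOVA", followed by post hoc tests. No other test of the training effect is stated. The correlations and the linear regression concern association among the variables.

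Sample section: "These volunteers will be randomly divided into two groups (control = C and experimental = E) of 13 volunteers each".

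Methods/Design section, on the first reassessment: "Outcomes will be measured again after ten weeks to reflect the immediate effect of the intervention". At that visit group E has trained and group C has not. On the last assessment: "Outcomes will be measured again to reflect longer-term outcomes from experimental group and the immediate effect of the intervention in the control group".

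The same section says what the crossover is for: change can be shown to be "specifically due to the intervention, and not due to the time factor and/or changes in the aging process".

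The Sample size section refers to a crossover design analysed by ANOVA with two degrees of freedom, and to "a bilateral hypothesis test" at the 0.05 level. It does not list the terms of that ANOVA.

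**The concern.** The levels of the stated comparison are occasions relative to training, and a change across them mixes the effect of training with anything else that changes over the same weeks. Candidates are regression to the mean in women selected on a threshold classification, practice on the Timed Up and Go and on maximal-effort dynamometry, season, and assay drift. The design has the remedy, because for the first ten weeks a randomised group goes untrained and is measured at the same visits. The written comparison does not call on that group.

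The trial's causal conclusion is at stake. An analyst who follows the sentence literally would test for a time effect, and a significant result would be read as a training effect.

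**Working it through.** **1. Which data fill the stated levels.** The second period is taken to last ten weeks, because group C receives the same program.

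| Group | Week 0 | Week 10 | Last visit (about week 20) |
|---|---|---|---|
| E (13) | before | after | follow-up |
| C (13) | untrained baseline | before own training | after own training |

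Group C has no follow-up value in the text. A within-woman comparison over all three levels is complete in at most 13 women, all in one arm and with no control. A two-level version can use 26 women (E: weeks 0 to 10; C: week 10 to last visit), but it is a pooled before-after test. Indexing time to each woman's own training is an inference. It is the reading under which before and after the intervention can apply to group C.

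**2. Does the sample size calculation reveal a group term?** Inputs from the Sample size section are effect size 0.5 (read here as Cohen's f), 2 numerator df, alpha 0.05, power 80% and a stated 13 per group.
- One-way ANOVA with three levels: noncentrality = f² × 3n = 0.25 × 3 × 13 = 9.75 on 2 and 36 df. Power is 76.9%; n = 14 gives 80.3%. The stated 13 is thus approximately reproduced.
- Two groups at one time: noncentrality = 0.25 × 2 × 13 = 6.5 on 1 and 24 df. Power is 68.7%, and 17 per group are needed.
- A 2 × 3 group-by-time interaction also has (2−1)(3−1) = 2 numerator df.

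Two degrees of freedom therefore fit either model. The calculation neither shows nor rules out a group term.

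**3. Illustration of the cost.** The documents give no SD, drift or within-woman correlation, so these are assumptions: no training effect, drift δ in SD units across the training period, correlation ρ of 0.5 or 0.7, two-sided 0.05.

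The paired test has standardised mean change dz = δ / √(2(1−ρ)) and noncentrality dz × √n on n−1 df. Example: δ = 0.3, ρ = 0.5, n = 26 gives dz = 0.3 / √1 = 0.30, noncentrality 0.30 × √26 = 1.53 and a rejection rate of 31.3%. With ρ = 0.7, dz = 0.3 / √0.6 = 0.387, noncentrality 1.97, rejection rate 47.6%.

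| Shared drift | n = 26, ρ 0.5 / 0.7 | n = 13, ρ 0.5 / 0.7 |
|---|---|---|
| 0.1 SD | 7.8% / 9.7% | 6.3% / 7.1% |
| 0.2 SD | 16.5% / 24.5% | 10.2% / 13.8% |
| 0.3 SD | 31.3% / 47.6% | 16.9% / 25.1% |

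In E versus C at week 10 a shared drift δ enters both groups: (0 + δ) − (0 + δ) = 0. The false-positive rate stays at 5%.

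**4. Drift confined to the first ten weeks.** Selection effects and first-retest gains would fall mainly between weeks 0 and 10 in both groups. They would then enter only group E's before-after change. With 0.3 SD in E and 0 in C, the pooled test rejects in about 11% (ρ 0.5) to 15% (ρ 0.7) by simulation. The week-10 contrast still cancels the drift.

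**5. Cross-check by simulation** (20,000 runs, linear drift of 0.25 SD per ten weeks, ρ 0.5 to 0.7): three-occasion ANOVA in group E alone 31% to 49%; pooled before-after 23% to 36%; E versus C change at week 10 about 5%; group-by-time over three occasions about 5%.

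**The case against.** The strongest reply is that silence is not exclusion. The sentence lists variables and occasions and then names ANOVA. It does not say that groups will not be compared, and an article commonly leaves model terms to a fuller plan. The Sample size section speaks of a crossover ANOVA, and its two degrees of freedom fit a 2 × 3 interaction. A reader might infer that the plan has rejected the randomised comparison. The documents do not support that, and this point does not claim it. What remains is that the article does fix a comparison, that its levels are times relative to training, and that neither section names a term that would use the control group.

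The size also needs care. A reader might take 48% as the expected error rate. It is the top of a range and assumes 0.3 SD of drift in all 26 women across their own training. Group C has been tested twice before it trains, the two groups train in different ten-week blocks so a seasonal shift need not be shared, and the dynamometer test includes familiarisation repetitions. All of these argue for smaller figures, such as the 11% to 15% in step 4. Inflation remains above 5% in every case shown with drift.

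The schedule in step 1 is read from the text alone, because Figure 1 is not available in the material reviewed.

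Finally, week-10 ANCOVA is not the only valid remedy. A group-by-time test also uses the randomisation.

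**Conclusion.** The point holds as a mismatch between the stated comparison and the stated claim. Followed as written, the ANOVA cannot support "This allows verification of the existence of a change and/or variable correlations specifically due to the intervention, and not due to the time factor". The design and the planned data can; the fault lies in the contrast that the article fixes.

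Under the assumptions in step 3, false positives run from about 8% to 48% for the pooled before-after test in 26 women, and from about 6% to 25% for a before-after test in 13. They are about 11% to 15% for the pooled test if a 0.3 SD drift touches only group E's training period, and 5% for the randomised contrast. These figures illustrate the mechanism and do not estimate this trial's error rate. That the comparison mixes time with training follows from the text and does not depend on them.

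**What to change.** Name the randomised comparison as the test of the training effect. Either of these would do:
- E versus C at week 10, as randomised, by ANCOVA with the woman's baseline value as covariate, reporting the adjusted difference and 95% CI, with cytokines on the log scale if skewed; or
- the group-by-time interaction over baseline and week 10.

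Report the within-woman before, after and follow-up comparisons as secondary and uncontrolled.

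Restate the power for the chosen contrast at 13 per group. ANCOVA has noncentrality d / √(1−ρ²) × √(13/2) on 23 df. The group-by-time test on two occasions has d / √(2(1−ρ)) × √(13/2) on 24 df. Neither value of d below is stated by the protocol, which gives only an effect size of 0.5 without saying on which scale. For two equal groups f = 0.5 corresponds to d = 1.0.

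| Effect | Unadjusted week 10 | ANCOVA, ρ 0.5 / 0.7 | Group-by-time, ρ 0.5 / 0.7 |
|---|---|---|---|
| d = 1.0 | 69% | 80% / 93% | 69% / 88% |
| d = 0.5 | 23% | 29% / 40% | 23% / 35% |

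The cost is a sentence or two of analysis wording and a revised power statement. Both groups are already measured at baseline and week 10, so no new visits or assays are needed. If the sponsor powers for the smaller effect, the restated power will show that 13 per group is too few, and that would have to be faced openly.
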